### 2.5. Standard Care

Participants originally allocated to the CG will pursue their usual care for 8 weeks.

Standard care for children with CP in Italy is provided primarily through the Italian National Health Service, which ensures access to care through a network of public and accredited rehabilitation facilities. The model of care is coordinated and multidisciplinary, typically involving professionals in child neuropsychiatry, physiotherapy, childhood neuromotor development therapy, speech and language therapy, psychology, orthopaedics, and social services. Despite the broad availability of services, access and quality of care may vary across regions due to differences in resource allocation, staffing, and waiting times. Moreover, the dose and the content of the standard care are often negligible in having a meaningful impact on the short-term outcome, particularly among adolescents. Due to ethical reasons, it is not possible to ask to interrupt the traditional standard care, and in this sense, the participation in the ACT ON DIP project does not intend to interfere with the traditional care, so no other standard intervention will be forbidden to participants of both groups.

During this period, participants will be asked to wear Actigraphs on both wrists.

Families of children in both groups will be asked to complete a daily diary during the 8-week training period, providing details regarding the frequency, duration, and type of all the main therapies, routines, and activities performed. The diary will have a daily checklist of the most common daily life activities, wake-up and school times. The daily diary will also include a guide on correctly using and managing the given wearable sensors.

### 2.6. Outcome Measures

Participants of both groups will undergo a series of tests commonly used in clinical practice, with a total duration of approximately 2 h. The evaluation will consist of clinical tests, questionnaires, and a technological part. All tests will be administered at all timepoints, unless otherwise specified. The evaluation will be structured as follows:

*Clinical assessment measures:*
Both Hands Assessment (BoHA [42]), identified as the primary outcome measure. It is an evaluation tool specifically designed to measure bimanual upper-limb performance in children with bilateral Cerebral Palsy.Melbourne Assessment 2 (MA2 [43]). It is a standardized tool designed to assess upper-limb movement quality in children with neurological impairments, aged between 2.5 and 15 years. It is carried out for each UL separately.Box and Block Test (BBT [44]). It is a quick and simple assessment tool for evaluating manual dexterity, with the two sides tested separately.

During these UL tests, participants will be required to wear Actigraphs on each wrist (described below).

Corsi Test [45]. This test is used to evaluate visuospatial memory and working memory. It will be administered as part of the assessment process at baseline (T0) and following training at T1 and T3.NEPSY II—Imitating Hand Positions subtest [46]. This subtest assesses the child’s ability to observe and replicate hand and finger positions demonstrated by the examiner, using both the dominant and non-dominant hand.NEPSY II—Manual Motor Sequences [46]. It involves imitating a series of rhythmic motor sequences using one hand or both.

*Parent-reported questionnaires, which will be administered to a parent or a caregiver:*
BRIEF-P/BRIEF-2 [47,48]. This standardized questionnaire is used to indirectly assess executive functions in children and adolescents based on observations by parents or teachers. Parents are asked to answer this questionnaire at baseline (T0) and following training at T1 and T3.ABILHAND-Kids [49]. This brief questionnaire is designed to assess the reported difficulty in 21 key bimanual daily activities.Canadian Occupational Performance Measure (COPM [50]). This validated tool is designed to identify rehabilitation needs in daily activities and any changes in performance, as reported directly by the individual or their family members. While this test is intended for caregivers and parents, collaborative children may also participate.Cerebral Palsy Quality of Life Questionnaire for Children (CP QOL–Child, 4–12 years [51]) and Cerebral Palsy Quality of Life Questionnaire for Adolescents (CP QOL–Teen, 13–18 years [52]). These questionnaires are designed to assess the quality of life of children and adolescents with Cerebral Palsy. This measure will be taken at T0 and T3. In the case of children older than 9 years, the self-reported form will be administered directly to the child/adolescent in addition to the primary caregiver version.Participation and Environment Measure—Children and Youth (PEM-CY [53]). This is a questionnaire that evaluates the child’s participation in the main environments they engage with, such as home, school, and the community. This assessment will be conducted at T0 and T3.Questionnaires for training compliance. In order to investigate the feasibility of the system and the compliance of children and their families, ad hoc questionnaires will be administered at the end of the training during the T1 assessment in the experimental group to three different stakeholders: the child, the primary caregiver who assisted the training, and the clinician.

In addition, an evaluation will be conducted using technological tools at all timepoints:

*Use of the Actigraph in daily life.*

The recruited participants will be asked to wear two Actigraphs (wGT3X-BT) on both wrists, during training sessions and during daily life. During this period, parents or participants will be required to fill out a diary recording the main daily activities.

*Measurement of manual skills using technological systems*

A subgroup of children will carry out also other technological assessments with the Virtual Reality Rehabilitation System (VRRS). The measurement of manual skills will be carried out through a set of evaluative VRRS tasks, aimed at quantitatively and objectively estimating and measuring manual abilities using kinematic movement parameters. Furthermore, the Upper Limb TRAcker (ULTRA+) biomechatronic system will be used to measure manual skills. This system provides measurements of both kinematic parameters and grip force.

Technological analysis, along with test and questionnaire scoring, will be conducted after the completion of all timepoint assessments. To maintain study blindness, the tests and questionnaires will be scored by personnel not directly involved in the training or SC supervision, i.e., personnel blind to the allocation group and the timepoint. When this is not be possible, all required data will be anonymized and randomized in order to hide the assessment timepoint.

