**Abstract:**

**Background**: Children with diplegic Cerebral Palsy often exhibit upper-limb (UL) motor impairments compounded by deficits in visuospatial, sensory, and executive functions. Despite this, research has primarily focused on lower-limb rehabilitation, leaving the treatment of UL function in diplegic Cerebral Palsy underexplored. Action Observation Therapy (AOT), based on Mirror Neuron System activation, has shown promise in promoting motor recovery, but evidence specific to this population is limited. This exploratory randomized controlled trial (RCT) aims to assess the feasibility and effectiveness of a home-based AOT program—ACT ON DIP—for improving upper-limb function in children and adolescents with diplegic Cerebral Palsy. **Methods**: Fifty-four participants with spastic diplegic Cerebral Palsy (MACS and GMFCS levels I–III, aged 5–16 years) will be randomly assigned to an experimental group (receiving an 8-week home-based AOT program) or a control group (receiving standard care). The ACT ON DIP system includes an ad hoc software, kits of objects for daily tasks, and wearable sensors. The system allows for delivering structured uni- and bimanual AOT activities tailored to the child’s profile. Primary outcome is the Both Hands Assessment (BoHA); secondary outcomes include motor (MA-2, BBT, ABILHAND), neuropsychological (NEPSY-II, Corsi Test, BRIEF), and participation measures (COPM, PEM-CY, CP-QOL). A subgroup will undergo fMRI to explore neural correlates of training-related changes. **Results**: Feasibility, compliance, and user experience with the home-based system will be assessed. This study will evaluate short-, medium-, and long-term changes in UL performance and related neuropsychological functions. **Conclusions**: ACT ON DIP represents a novel, personalized, and accessible tele-rehabilitation intervention for children with diplegic Cerebral Palsy. If effective, it could expand treatment opportunities for UL rehabilitation in this population and support broader implementation of home-based AOT.

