In addition, few studies have explored the effects of rehabilitation on the structure and function of the central nervous system in children with CP, such as a recent study [35], which observed brain modifications correlated with functional improvements in children with unilateral CP. Another study reported that, in children with unilateral CP, AOT treatment based on the observation and imitation of pathological models—that is, other children with CP—leads to increased activation of the Mirror Neuron System, as well as enhanced activation of subcortical areas such as the sensorimotor thalamus [36].

New Information and Communication Technologies (ICTs) represent one of the most promising means of offering personalized rehabilitation interventions directly in the patient’s home environment; they also allow continuous monitoring of treatment by clinical staff and enhance the motivation of the participants [37]. As highlighted by recent studies [32,38], it is therefore possible to use new technologies to deliver AOT treatments directly to patients’ homes. In fact, the use of technological platforms allows a large number of patients to have access to innovative, intensive, and personalized treatments in their home environment. Further investigation, particularly randomized controlled trials (RCTs), is needed to better understand the mechanisms of brain plasticity in children with neurological injuries. In fact, larger and more rigorous studies could help strengthen the scientific evidence supporting innovative training such as AOT, enabling the standardization of its use and the identification of individual factors, in order to develop personalized approaches.

Within this framework, the ACT ON DIP project (ACTion Observation tele-rehabilitatioN for upper limb in children with DIPlegic Cerebral Palsy), designed as an exploratory RCT, aims to first assess the feasibility and then to investigate the effectiveness of UL AOT training on children and adolescents with diplegic CP. Specifically, the AOT will be provided at home by means of a dedicated technological system.

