### 2.3. Sample Size

For the present study, a minimum size of 21 subjects per group is required to obtain a difference of at least 5 BoHA units at a significance level of 0.05 and a power of 80%. Considering a possible dropout of 20%, at least 27 subjects per group will be recruited, for a total sampling of at least 54 children with diplegic Cerebral Palsy. The minimum sample size was computed using the G*Power software v 3.1 9.6.

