#### 2.4.1. ACT ON DIP System

The ACT ON DIP system is designed through the collaboration of clinical rehabilitation staff, including physicians, therapists, and psychologists from IRCCS Fondazione Stella Maris, AUSL IRCCS of Reggio Emilia, and the University of Parma, in partnership with engineers and Khymeia (Italy). The main components of the ACT ON DIP system, the exercise library, and the experimental training were built based on previous clinical experiences with UPCAT and TELE-UPCAT.

The ACT ON DIP system, shown in Figure 2, consists of an all-in-one computer, with an ad hoc software, which includes the AOT video library, two age-appropriate narrative contexts that guide the training for children and adolescents (conceptualized and created in collaboration with the FTS foundation), and specific instructions for each training day and activities.

The ACT ON DIP system software operates as follows: a video of the daily task is presented to the participant, after which the participant is asked to execute the action shown in the video. Then, the same video is replayed, and the participant executes the action a second time. At the end of each session, the software automatically loads the next day’s task, uploads the recorded videos to a secure cloud service for clinician review, and shuts down.

A mascot is used to create a narrative context, which guides the patient throughout the training session. It presents the activities, keeps the patient focused on the task, and gives visual rewards.

The system is equipped with two cameras: one to capture the execution phase, providing a comprehensive view of the child, the table, and the object, and another to record the observation phase, focusing on the child’s face and determining whether they are looking at the monitor. To ensure that participants are paying attention to the screen contents, they will be required to wear an IMU sensor inside a headband that will record head movements during the observation phases. Participants will also be asked to wear a pair of wearable sensors (described below) for registering UL movements. Supporting caregivers will also be given a sensor that communicates with the system and allows the activities to progress.

Together with the ACT ON DIP system, the same objects shown in the videos will be provided to the family, as well as the related placemats to facilitate initial object positioning.

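### The only measure tied to feasibility, the first stated aim, is a questionnaire at T1, so families who leave the experimental group before T1 are not counted

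*Protocol article*

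**What the plan says.** The Introduction states that the project "aims to first assess the feasibility and then to investigate the effectiveness of UL AOT training", and the Discussion keeps that order. The Abstract adds that "Feasibility, compliance, and user experience with the home-based system will be assessed", without naming a measure.

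Section 2.6 names one. It opens with the purpose, "In order to investigate the feasibility of the system and the compliance of children and their families", and then fixes the timing and the arm: "ad hoc questionnaires will be administered at the end of the training during the T1 assessment in the experimental group". The respondents are "the child, the primary caregiver who assisted the training, and the clinician". No other measure in the article is tied to feasibility or compliance.

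Three other parts of the article bear on the point:

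- **Losses are foreseen.** Section 2.3 says: "Considering a possible dropout of 20%, at least 27 subjects per group will be recruited". Section 2.2 lists conditions under which participants are removed from the study.
- **Session-level data exist.** Section 2.4.1 says that at the end of each session the software "uploads the recorded videos to a secure cloud service for clinician review". Section 2.5 describes a daily diary kept by families in both groups over the 8 weeks.
- **The load is set.** Section 2.4 plans one session a day of about an hour, 5 days a week for 8 weeks.

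**The concern.** Feasibility asks whether families offered the system can use it as intended. The natural denominator is therefore every child randomised to the experimental group. A questionnaire given once, at T1, has a different denominator: those still in the study at T1. Daily sessions over 8 weeks are a plausible reason to leave, so absence at T1 may itself be a sign that the programme was not feasible for that family. If so, the families with the least favourable experience are over-represented among those not asked, and the summary leans towards a good result.

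Session counts are also a more direct measure of compliance than a rating collected at one visit. They exist for each child up to the point of stopping, and they do not depend on attending T1. The article describes the recordings that would supply these counts but does not use them for this aim.

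At stake is the reading of the first aim. A favourable feasibility statement that holds only for those seen at T1 is weaker support for wider use of the system than one covering all families who were allocated to it.

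**Working it through.** **Inputs.** From Section 2.3: 21 evaluable per group ("a minimum size of 21 subjects per group is required to obtain a difference of at least 5 BoHA units"), a 20% dropout allowance and 27 recruited per group. From Section 2.4: 5 sessions a week for 8 weeks. The number of positive respondents is not in the article and is assumed below.

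**Step 1: the plan's own figure.** n = 21 / (1 − 0.20) = 26.25, rounded up to 27 per group and 54 in total. This reproduces the article.

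**Step 2: planned dose.** 5 × 8 = 40 sessions per child, which is the natural denominator for compliance.

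**Step 3: how many could be missing at T1.** 0.20 × 27 = 5.4, so 5 to 6 families, leaving 22 or 21 respondents. This assumes that the whole allowance is used and falls before T1. The article gives neither the cause nor the timing of dropout.

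**Step 4: what the T1 answers can say about all 27.** Let m be the number missing at T1 and k the number of positive respondents. The rate among respondents is k / (27 − m). The rate over all randomised lies between k / 27 (every missing family negative) and (k + m) / 27 (every missing family positive). With roughly 90% of respondents positive (assumed):

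| Missing before T1 | Positive / respondents | Rate at T1 | Lowest over 27 | Highest over 27 |
|---|---|---|---|---|
| 0 | 24/27 | 88.9% | 24/27 = 88.9% | 24/27 = 88.9% |
| 3 | 22/24 | 91.7% | 22/27 = 81.5% | 25/27 = 92.6% |
| 5 | 20/22 | 90.9% | 20/27 = 74.1% | 25/27 = 92.6% |
| 6 | 19/21 | 90.5% | 19/27 = 70.4% | 25/27 = 92.6% |

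**Step 5: reading the table.** The rate at T1 hardly moves, from about 89% to 92%. The range for all randomised widens from nothing to about 22 percentage points (92.6 − 70.4). The lower end is a worst case. If leaving has nothing to do with the system, the rate at T1 is close to right. The T1 answers alone cannot show which case applies. The table also treats feasibility as a yes/no rating. The article defines no such rating, so it is used here only to show the effect of the denominator.

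**The case against.** The strongest reply is that the text fixes a time and an arm and does not restrict the questionnaires to those who finish training. Section 2.1 has both groups assessed at T1, and the removal conditions in Section 2.2 do not include stopping or poor adherence to the training. A family that gives up the sessions but attends T1 can answer, and the clinician is a third respondent. This stands. A reader might infer that every family that stops training is left out, but the article does not support that. The gap concerns only those lost or removed before T1.

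The size is also open. The 20% is a sample-size allowance with no stated cause, and follow-up runs to 24 weeks after T1, so some of it may fall after T1. Some of the removal conditions need have nothing to do with the system. A reader might conclude that the result is certain to be biased upward, or that the trial cannot answer its first question. Neither follows: the bias may be small or absent, and the questionnaires do inform feasibility for those seen at T1.

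Finally, the article is condensed. Section 2.8 sets out no feasibility analysis, and a reader might count that as a fault. Such an analysis can properly sit in a fuller protocol or analysis plan that is not shown, so nothing is claimed from its absence. What remains is a stated choice: Section 2.6 says what the feasibility and compliance instrument is, when it is given and to whom. Nothing says that session videos and diaries will be ignored, but neither is named for this purpose.

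**Conclusion.** The point holds in a limited form. The one measure tied to feasibility and compliance is taken at T1 in the experimental group, so the first aim is answered only for those assessed at that visit. The result may be too favourable if leaving is related to the burden of the 40 sessions, which is plausible but not shown.

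The size cannot be derived from the article. If the whole 20% allowance fell before T1 and 20 of 22 respondents were positive (both assumed), the reported 91% would be compatible with 74% to 93% over all 27 randomised. With fewer early losses the range narrows, and with none it closes.

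This does not affect the BoHA comparison or the sample size, and no statement in the article is contradictory. It is a measurement choice for the first aim that can be improved at little cost.

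**What to change.** In Section 2.6, define compliance and feasibility as the number of the 40 planned sessions completed per child, counted from the session videos the system already uploads. Summarise it with a 95% confidence interval over all children randomised to the experimental group, with non-starters counted as zero and early stoppers included at the number they reached. Report beside it the number retained to T1.

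Keep the T1 questionnaires as user-experience data and state how many families answered out of those randomised. Where possible, offer the same questionnaire to a family when it stops.

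**Cost.** A change of wording, a little data extraction and one short form at early stopping. The article describes uploaded videos and not a completion log, so a short rule is needed for what counts as a completed session. The family diary can serve as a cross-check where an upload is missing.

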### 2.7. fMRI Task

An fMRI investigation will be performed at T0 and T1 on a subgroup of participants with diplegic CP in both EG and CG in order to assess MNS activation at baseline (T0) and training effects (T1 vs. T0). We will not perform these assessments at T2 and T3 because these measurement procedures are particularly time-consuming, and including children at all timepoints might discourage them from participating in the study. A baseline investigation will also be carried out in age-matched typically developing children.

#### 2.7.1. Experimental Procedure

Before each functional imaging session, participants will undergo a 15 min training session to familiarize themselves with the MR environment and the experimental procedure. Following this, participants will be invited to take part in the actual fMRI session, which will be divided into three short runs, each lasting approximately 8 min. Participants will be instructed to perform two types of experimental tasks: (a) action observation (functional run 1) and (b) motor execution (functional runs 2–3).

#### 2.7.2. Action Observation Task

During the first functional run, visual stimuli will be presented binocularly via Liquid Crystal Display (LCD) goggles (NordicNeurolab). Participants will watch short video clips (6 s each) showing unimanual or bimanual actions performed by an actor from a first-person perspective. The experimental conditions will be (a) observation of unimanual actions with the right hand, (b) observation of unimanual actions with the left hand, and (c) observation of bimanual actions.

The observed actions will involve grasping an object resembling a belt, which needs to be fastened using Velcro at the centre of a geometric object. The objects will have either a square or octagonal shape, comprising five distinct objects for unimanual actions and five for bimanual actions. Bimanual objects will differ by featuring two belts, in contrast with the single belt on the unimanual objects. To enhance visual variability, the objects will be presented in different colours.

The visual characteristics of each video (e.g., brightness, contrast, sharpness, and amount of visual information) will be balanced across conditions. A total of 20 video clips will be used (5 objects × 2 types × 2 shapes). During the functional run, videos will be presented in blocks of four (24 s per block). Each condition will include 4 blocks, totalling 16 repetitions of 6 s videos per condition. Each block will be followed by a 12 s rest period, during which participants will fixate on a white cross against a black background.

Four catch trials will be included to assess participants’ attention. In these trials, participants will be asked to identify the shape of the last object in the preceding video by choosing between two displayed options. Responses will be given by slightly moving one of the two hands.

